## **7.2.b PROTECTION OF STUDY INFORMATION**

### **CONFIDENTIALITY**

To protect study participants, data will be strictly confidential. Only study team members and study-related personnel will have access to participant's private health information / health information identifiers (e.g., first and last name, patient DOB, address and phone number) in order to schedule, run and conduct the study. Stanford University will share participants' identifying information and health information with the Cardiac Therapy Foundation only as necessary to conduct the study and to ensure participant safety.

All participants will be identified by a unique study ID, which will be generated as part of the study enrollment process. Data containing any identifying information such as a name or address will be kept separately from the study ID and other data collected for the study. Only the PI / study team will have access to the key code. No participant data will be stored on local drives or laptops.

Every effort will be made to keep identifying information confidential. Any printed materials containing information on participants (e.g., consent forms) will be stored in locked filing cabinets within locked offices, with access by the PI / study team only. No study participant will be identified individually in any publication. Participant names and identifiers will not be used in the publication or presentation of findings from this study.

Database development work, constructing data from multiple sources including primary data collection and entry, and EpicCare EHR, will be carried out by the SCCI/IMPACT analyst team. Database files will be maintained in a computer that will require passwords for access known only by study personnel. All data from study visits and intervention exercise sessions will be directly entered into the secure study database on a secure, password protected computer.

### **SECURITY AWARENESS TRAINING**

All study team members will receive training on policies regarding the confidential nature of the data collected, processed, and stored at Stanford, and must sign a confidentiality agreement before being allowed access to confidential information. The training will cover topics such as the HIPAA regulations, protection of participant rights, privacy and confidentiality, disposal of confidential material, etc. The Principal Investigator will also reinforce the confidential nature of all study data at study team meetings.

All study team members will receive training and pass requirements for conducting research on human subjects. The Stanford provides education and certification on human subjects research

through the Collaborative IRB Training Initiative (CITI), a web-based training package on issues relating to human subjects research. The CITI web site is maintained by the University of Miami, with content developed by a national consortium. Over 400 institutions use CITI for mandatory Protection of Human Subjects training. Successful completion of the CITI Basic Course is required of all faculty, staff, and students who are engaged in research activities at Stanford that involves human subjects.

#### **PROTECTION AGAINST DATA LOSS**

A backup of the study database will be made daily.

#### **MACLICIOUS CODE PROTECTION**

Stanford uses several techniques to protect against assaults by viruses, spy bots, worms and other malicious attacks.

## **Chapter 8: Data and Safety Monitoring Plan, Adverse Events, and Study Discontinuation**

## 8.1 DATA AND SAFETY MONITORING PLAN

### 8.1.a DATA AND SAFETY MONITORING BOARD

The IMPACT Study will utilize a Data Safety Monitoring Board (DSMB).

#### OBJECTIVES

The major goals of Data Safety Monitoring Board (DSMB) are to:

1. Review safety data, including but not limited to adverse events, serious adverse events (i.e., hemorrhage, death), and appropriateness of subject enrollment
2. Ensure protection of privacy
3. Ensure confidentiality of data
4. Assure intervention goals are being met

#### SIZE AND COMPOSITION

The DSMB will consist of 3 to 5 members both internal and external to the IMPACT team and consultants. The planned composition may include the following: Biostatistician (1), Exercise expert (1-2), and Clinician (1-2).

#### MAJOR RESPONSIBILITIES

1. Sign and abide by a statement of confidentiality
2. Disclose any actual or potential conflicts of interest
3. Familiarity with research protocol and plans for safety monitoring
4. Oversee safety of participants to include review of adverse events
5. Review reports of related studies, as appropriate
6. Review major proposed modifications

Following each meeting, the DSMB will provide written documentation regarding findings for the study as a whole and any relevant recommendations related to continuing, changing, or terminating the study.

#### APPOINTMENT OF MEMBERS

DSMB voting members are appointed by the Principal Investigator and/or her designee for a fixed term.

#### Meetings

DSMB meetings will take place annually (in-person) and on a quarterly basis (by teleconference) until there are no active participants in the study.

#### Recommendations

All DSMB recommendations are submitted to the Principal Investigator and/or her designee with a copy provided to NIH Program Director or designee.

## Reports

The frequency of data review for this study differs according to the type of data, the availability of the data collected, and the perceived level of risk.

| Data Type                                                                                                          | Frequency of Review |
|--------------------------------------------------------------------------------------------------------------------|---------------------|
| Recruitment (adherence to demographics and inclusion/exclusion stated in protocol)                                 | Quarterly           |
| Adverse event rates                                                                                                | Quarterly           |
| Compliance to intervention                                                                                         | Quarterly           |
| Statistical power implications due to dropouts and missing data                                                    | Annually            |
| Progression of diabetes, increases in blood pressure, and/or worsening of lipid profiles in the three study groups | Annually            |

## 8.2 REPORTING OF RECRUITMENT, ADHERENCE AND ADVERSE EVENTS

### 8.2.a RECRUITMENT, ADHERENCE AND COMPLIANCE

#### RECRUITMENT AND ADHERENCE

Review of the rate of recruitment as well as adherence to inclusion or exclusion criteria occurs annually to confirm that participants meet the eligibility criteria as stated in the grant proposal.

#### PARTICIPANT COMPLIANCE

Interventionists monitor participant compliance to the intervention protocol on a weekly basis. This data is shared with the Principal Investigator, Research Coordinator, Statistician, and the Safety Officer. If the Safety Officer has any concerns about the compliance inhibiting the ability of the study to test the primary outcome, study investigators will be contacted and methods for improving compliance will be discussed.

### 8.2.b ADVERSE EVENTS

Adverse events will be presented to the Study Principal Investigator, Statistician, Chair of the Stanford University Institutional Review Board. Adverse event data from the intervention groups will be analyzed quarterly. The IMPACT Study anticipates most adverse events will be mild and the participant will be able to resume intervention activities within a day or two of reporting the event.

#### DEFINING ADVERSE EVENTS

By definition, an adverse event is any unfavorable or unintended sign or symptom temporarily associated with the medical assessment or procedure or the intervention.

#### Event Classification

Adverse events are categorized based on event outcomes.

1. Serious Adverse Event – Any event that results in the following outcomes: Death, risk of death (life-threatening), in-patient hospitalization or prolongation of hospitalization, a persistent or significant disability or incapacity, or congenital anomaly or birth defect.
2. Unexpected Adverse Event – Any adverse event, the specificity or severity of which is not an expected consequence of the medical treatment or procedure.

### **Event Attribution**

Adverse events may also be defined by attribution. Attribution refers to the determination of whether an adverse event is related to a medical treatment or procedure. The categories for attribution are as followed:

1. Definite – The adverse event *is clearly related* to the medical treatment or procedure.
2. Probable – The adverse event *is likely related* to the medical treatment or procedure.
3. Possible – The adverse event *may be related* to the medical treatment or procedure.
4. Unlikely – The adverse event *is doubtfully related* to the medical treatment or procedure.

### **Event Severity**

For the IMPACT Study, adverse events will be further graded according to severity. Appropriate actions related to participant well-being and study intervention will be taken according to the severity of the event.

#### ***Grade 1: Mild Adverse Events***

A mild adverse event includes slight muscle soreness or stiffness that does not limit daily activity. Modifications to an intervention are not needed for a Grade 1 adverse event. More frequent evaluations may be required until the adverse event resolves or the study participant stabilizes.

#### ***Grade 2: Moderate Adverse Events***

Moderate adverse events include severe muscle soreness or stiffness resulting in a limitation in daily activity. Study participants who develop Grade 2 adverse events may continue to exercise at full protocol prescription. However, the intervention may be modified until the adverse event resolves. In addition, more frequent evaluations may be required until the adverse event resolves or the study participant stabilizes.

#### ***Grade 3: Severe Adverse Events***

Severe adverse events include severe muscle soreness or stiffness that results in limited daily activity. Severe adverse events also include other physical events including, muscle strain, ligament injury, intermittent claudication, development of transient but reproducible dyspnea, chest discomfort, or lightheadedness. The intervention for study participants who develop Grade 3 adverse events will be modified until the adverse event returns to Grade 1 or less. More frequent evaluations may be required until the adverse event resolves or the study participant stabilizes.

If a severe adverse event persists despite a modified intervention, the intervention may be interrupted for up to a maximum of 2 weeks. If the intervention must be interrupted for more than 2 weeks, the participant may be permanently discontinued from the study. If the adverse event resolves within the 2 weeks, the modified intervention may be restarted. A study participant who tolerates the modified intervention for at least 2 weeks can then be increased to the full intervention.

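### Grade 2 and Grade 3 describe the same muscle soreness event, but reducing exercise is optional under one and mandatory under the other

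*Protocol*

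**What the plan says.** Section 8.2.b of the protocol defines four severity grades. Under Event Severity it makes the grade operative: "Appropriate actions related to participant well-being and study intervention will be taken according to the severity of the event". Soreness appears in three of the four grades.

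- Grade 1 (mild): "A mild adverse event includes slight muscle soreness or stiffness that does not limit daily activity". No change to the exercise is needed.
- Grade 2 (moderate): "Moderate adverse events include severe muscle soreness or stiffness resulting in a limitation in daily activity". The participant "may continue to exercise at full protocol prescription". The next sentence adds: "However, the intervention may be modified until the adverse event resolves".
- Grade 3 (severe): "Severe adverse events include severe muscle soreness or stiffness that results in limited daily activity". The intervention "will be modified until the adverse event returns to Grade 1 or less". If the event persists despite modification, exercise may be stopped for up to 2 weeks. If a longer stop is needed, the participant may be discontinued permanently. Someone restarted on modified exercise who "tolerates the modified intervention for at least 2 weeks can then be increased to the full intervention".

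Grade 4 lists no soreness. Grade 3 also lists strains, ligament injuries and exertional symptoms, none of which is in Grade 2.

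**The concern.** The grade decides what staff do with the participant's exercise, so each event needs one grade. Severe soreness that limits daily activity has two. Under Grade 2 staff may leave the participant on the full programme; under Grade 3 they may not. Soreness is a foreseeable effect of the resistance training in this trial, and section 1.2.a rests much of the case for supervised exercise on preventing injury. The rule for when to back off therefore ought to be clear.

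There is a smaller reporting consequence. Adverse event data from the intervention groups are analysed quarterly (section 8.2.b), and the DSMB reviews event rates quarterly (section 8.1.a, Reports). If either review split soreness into Grade 2 and Grade 3, the split would reflect which paragraph the grader had used.

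**Working it through.** The protocol states no figure to reproduce here. The check is a comparison of the grade definitions, followed by some simple counts.

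**Step 1: definitions and actions side by side (section 8.2.b)**

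| | Grade 1 | Grade 2 | Grade 3 |
|---|---|---|---|
| Soreness intensity | slight | severe | severe |
| Limits daily activity | no | yes | yes |
| Full prescription allowed | yes | yes | no |
| Modification | not needed | optional | mandatory until Grade 1 or less |
| Interruption | none stated | none stated | up to 2 weeks if the event persists |
| Permanent discontinuation | none stated | none stated | possible if more than 2 weeks are needed |

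The first two rows are identical for Grades 2 and 3; the remaining rows are not.

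**Step 2: is there a separating criterion elsewhere?** Section 8.2.b, the early discontinuation list in 8.3.a and the stopping rules in 8.3.b give no duration, degree of limitation or other test that would tell Grade 2 soreness from Grade 3 soreness.

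**Step 3: what the soreness wording covers.** Cross intensity (slight, moderate, severe) with limitation (no, yes): 3 × 2 = 6 combinations.

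| Intensity | Not limiting | Limiting |
|---|---|---|
| Slight | Grade 1 | none |
| Moderate | none | none |
| Severe | none | Grades 2 and 3 |

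One combination is named once, one is named twice, and four are not named, including both moderate ones. This grid is a device of this review; the protocol does not claim to list every case.

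**Step 4: who is subject to the rule.** Section 6.2.b plans 115 per arm and 345 in total. Two arms exercise: 2 × 115 = 230 of 345. This is the number with an exercise prescription, not the number expected to have the event.

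**Step 5: how far apart the two actions can be.** Grade 2 requires 0 weeks below full prescription. Grade 3 requires modification until the event falls to Grade 1 or less, with no stated minimum duration if exercise is not interrupted. If the event persists and the whole 2-week interruption is used, at least 2 weeks of modified exercise follow: 2 + 2 = at least 4 weeks. The programme lasts 26 weeks (section 4.2.a), so 4 / 26 = 15.4%. This is a conditional path, not a forecast.

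**The case against.** The strongest reply is that this is probably a one-word slip, with moderate intended in a paragraph headed moderate, and that it does little harm. Staff who modify the exercise satisfy both paragraphs. The overlap covers one event type. The grade texts give examples and are not exhaustive, so a combination that is not listed is not thereby ungraded, and the absence of moderate soreness is the same slip seen from the other side. The comparison of 0 with 4 weeks sets a minimum against an extreme path. No Grade 2 versus Grade 3 table of soreness is planned, and seriousness, reporting deadlines and removal criteria do not use this boundary. Trained instructors, repetition ranges, alternate exercises, the 8- and 16-week evaluations and individual review of withdrawals all make unchecked full-dose exercise less likely.

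Most of this stands as a limit on the size of the point. The slip is the likely origin, though that is an inference. The grid, the 230 and the 4 weeks are illustrations, and the conclusion does not need them. What the reply does not supply is a way to choose between the two grades. Clinical judgement and supervision soften the consequence, but they do not make staff apply a self-contradictory rule in the same way. That modification satisfies both paragraphs shows only that the cautious choice is available; the Grade 2 text still permits the other one.

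**Conclusion.** The point holds, and the text is wrong as written. One event, severe soreness or stiffness limiting daily activity, falls in two grades with different rules: modification is optional in one and mandatory in the other. This is an internal contradiction in a participant-safety rule and not detail left for a later document, because grade definitions and exercise modification belong in the protocol.

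Its reach is limited. It concerns soreness and stiffness only, in the two exercise arms. The protocol expects most adverse events to be mild and gives no rate for severe soreness, so the number of participants affected cannot be estimated. Total adverse event counts, the 24- and 48-hour reporting rules, the primary analysis, sample size and power do not depend on it. It should be corrected because it bears directly on how participants are managed and is cheap to put right. The conclusion rests only on the ordinary meaning of the two definitions and on the statement that action follows severity.

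**What to change.** Amend the Grade 2 and Grade 3 paragraphs of section 8.2.b so that their soreness criteria do not overlap, for example:

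- Grade 2: moderate soreness or stiffness with some limitation of daily activity.
- Grade 3: severe soreness or stiffness that limits daily activity.

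Add that the higher grade applies in doubt. With this wording no combination in the grid carries two grades. Slight non-limiting soreness stays in Grade 1, and moderate limiting and severe limiting soreness each have one grade. The other three (slight limiting, moderate non-limiting, severe non-limiting) fall to the in-doubt rule. The study physician and Safety Officer should confirm the boundary and state the grade for those three, in particular whether severe but non-limiting soreness should trigger mandatory modification.

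Re-grade any soreness already recorded as Grade 2 or Grade 3 where the records allow, and note where they do not.

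The cost is a short text amendment, a notice to staff and, if events are already on file, a brief re-grading exercise. Visits, sample size and reporting deadlines do not change.

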#### ***Grade 4: Life-Threatening Adverse Events***

Life-threatening adverse events include bone fracture or development of refractory myocardial ischemia, dyspnea, and clinically relevant contraindications for exercise as outlined by the American College of Sports Medicine. Study participants who develop Grade 4 adverse events will have their intervention discontinued permanently. The study participant will return for a follow-up evaluation as clinically indicated or in a maximum of 2 weeks and should remain under medical observation until the adverse event resolves or the study participant is stabilized.

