### Examples of IMPACT Study-Related Adverse Events

Examples of specific adverse events, which require immediate reporting include, but are not limited to the following:

1. Life-threatening adverse events
2. Inpatient hospitalization
3. Prolongation of an existing hospitalization
4. Disability
5. Occurrence of chest pain
6. Intermittent claudication
7. Cardiac or pulmonary complications as recommended by the American College of Sports Medicine
8. Any death that occurs while the patient is enrolled in the study including the follow-up period, or within 30 days of completing the study.

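### The Grade 3 rule lets exercise continue or restart after chest discomfort, reproducible dyspnea, claudication or lightheadedness without requiring a clinician's evaluation

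*Protocol*

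**What the plan says.** Protocol section 8.2.b grades adverse events and ties an exercise action to each grade. Besides severe soreness, Grade 3 lists "muscle strain, ligament injury, intermittent claudication, development of transient but reproducible dyspnea, chest discomfort, or lightheadedness".

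One sequence applies to all of them:

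- At onset the intervention "will be modified until the adverse event returns to Grade 1 or less".
- If the event persists despite modification, exercise may be interrupted, for 2 weeks at most. Beyond that, the participant may be permanently discontinued from the study.
- After an interruption: "If the adverse event resolves within the 2 weeks, the modified intervention may be restarted".
- Finally: "A study participant who tolerates the modified intervention for at least 2 weeks can then be increased to the full intervention".

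The Grade 3 text says that more frequent evaluations may be required. It does not say who performs them, and it does not make them a condition of restart.

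Grade 4 is handled differently. It includes "development of refractory myocardial ischemia, dyspnea, and clinically relevant contraindications for exercise as outlined by the American College of Sports Medicine", and the rule there is: "Study participants who develop Grade 4 adverse events will have their intervention discontinued permanently".

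**The concern.** Resolution and tolerance are sensible tests for a strained muscle. They are weaker tests for a symptom that may be cardiac, pulmonary or vascular. A symptom that is transient but returns with effort subsides between bouts, and it may ease simply because the load was reduced. Under the Grade 3 rule, that easing is what allows exercise to resume.

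At stake is the safety of individual participants. Someone with new chest discomfort may be reported and seen acutely, yet the exercise rule does not wait for the outcome. As written, modified exercise goes on from onset, and no clinician has to record that this is safe. Entry screening lowers the starting risk but cannot assess a symptom that first appears during the program.

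**Working it through.** The protocol states no figure on this point, so the check is mainly a reading of every provision that could supply the missing evaluation. A short calculation then prices the remedy.

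**Does any other provision require a clinician's evaluation before exercise continues or restarts?**

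| Protocol section | What it provides | Condition of continuing or restarting exercise? |
|---|---|---|
| 3.2.b Exercise Stress Test; 4.1.b footnote on PCP clearance | Stress test and PCP clearance before enrollment | No, entry only |
| 4.2.a Exercise Evaluations | Fitness evaluations before the start, at 8 weeks and at 16 weeks | No, fixed times, not triggered by an event |
| 4.2.a Instructors | Sessions led by trained CTF staff | No |
| 5.2.a | Study physician or nurse may decide on withdrawal, reviewed individually as temporary or permanent | No, discretionary and not triggered by a Grade 3 symptom |
| 5.2.b | Physician or nurse notified of events at a study visit; Fast Track, 9-1-1, notice to the PCP | No, acute care and notification |
| 8.2.b Grade 4 | Permanent stop | Not applicable, no restart |
| 8.2.b reporting examples | Immediate reporting, with chest pain and claudication on the list | No |
| 8.3.a | Removal for serious events or serious illness, or at the investigator's judgement | Not applicable to a non-serious event that stays in the program |

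The reporting list is introduced by "Examples of specific adverse events, which require immediate reporting include, but are not limited to the following". It shows that the protocol already treats chest pain and claudication as more than soreness, but it governs reporting and not exercise.

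What remains is a Grade 3 symptom of this kind that is neither serious nor Grade 4. For that case the only stated conditions are resolution (restart) and at least 2 weeks of tolerance (step-up).

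**How many participants fall under the rule?** Section 6.2.b plans 115 per arm, and two arms exercise: 2 × 115 = 230. This is the population covered, not the number affected.

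**What would a hold cost in sessions?** Inputs: 26-week program (4.2.a), 1 or 3 sessions per week (2.2.a), adherence defined as attending more than 80% of assigned sessions (6.2.a).

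- Assigned sessions: Arm 1, 26 × 1 = 26; Arm 2, 26 × 3 = 78.
- Missed in a 2-week hold: Arm 1, 2 × 1 = 2; Arm 2, 2 × 3 = 6.
- Attendance with no other misses: 24/26 = 92.3%; 72/78 = 92.3%.
- Most sessions that can be missed while staying above 80%: Arm 1, 5 (21/26 = 80.8%, but 20/26 = 76.9%); Arm 2, 15 (63/78 = 80.8%, but 62/78 = 79.5%).
- In time, that is 5/1 = 5 weeks in Arm 1 and 15/3 = 5 weeks in Arm 2, if nothing else is missed.

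**The case against.** The strongest reply is that the rule is permissive and other safeguards surround it. Restart and step-up are allowed, not required, so staff may hold back. Under 5.2.a a study physician or nurse can impose a temporary withdrawal after individual review, which works much like a hold. Section 2.4.c excludes people with past or present cardiovascular problems or respiratory disease, in addition to the stress test. All of this stands and narrows the gap. It does not close it, because none of it is triggered by the symptom or required before exercise goes on.

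A reader might also infer more than the text supports:

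- *That every participant with chest discomfort or dyspnea keeps exercising.* The Grade 4 rule stops exercise permanently for clinically relevant ACSM contraindications. That list is not in the protocol, so some cases may leave Grade 3. The point is limited to those that stay.
- *That the Grade 3 exit test sets no standard for these symptoms.* The Grade 1 text reads "A mild adverse event includes slight muscle soreness or stiffness that does not limit daily activity". The word for inclusion makes soreness an example, and the clause on daily activity is a functional marker. Full resolution also satisfies the test.
- *That the Grade 4 dyspnea wording should be limited to refractory dyspnea.* The sentence can be read either way, and the narrower reading is the less protective one.
- *That step-up needs its own clearance.* Once a physician has evaluated the symptom and cleared modified exercise, the existing tolerance step is a reasonable next stage.

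A further objection concerns the remedy. A hold pending evaluation could run past 2 weeks and so meet the limit beyond which a participant may be permanently discontinued. That is correct, and the change must deal with it.

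**Conclusion.** The point holds for Grade 3 chest discomfort, reproducible dyspnea, claudication and lightheadedness that are neither serious nor Grade 4. For these, exercise is modified rather than held at onset and may restart on resolution alone, with no clinician's evaluation required at either stage. This goes beyond missing detail: following the stated rule keeps a participant with a new symptom of this kind exercising before anyone has to evaluate it.

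The rule covers 230 planned participants for 26 weeks. How many would develop such a symptom cannot be derived from the protocol, and no rate is assumed. The session figures show that the remedy is affordable, not that harm is frequent. The change should be made. Confidence is medium, because the ACSM list and the discretionary review in 5.2.a may already catch some cases.

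**What to change.** Amend the Grade 3 text in section 8.2.b:

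1. Separate chest discomfort, reproducible dyspnea, claudication, and lightheadedness that is not promptly explained and corrected from the musculoskeletal events. Hypoglycemia is the obvious example of an explained cause, and 4.2.a already provides glucometers and fast-acting carbohydrates. The qualifier on lightheadedness is proposed here; the protocol lists the symptom without one.
2. For these symptoms, hold exercise at onset and require one documented evaluation and clearance by the existing study physician before modified exercise restarts. The present 2-week tolerance step to full exercise then applies.
3. State that a hold pending this clearance does not by itself count toward the 2-week limit after which a participant may be permanently discontinued, and that follow-up assessments continue during it. This matters because 6.2.a treats participants who cannot continue at their assigned frequency as lost to follow-up.
4. Leave the Grade 4 dyspnea wording as it is.

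The cost is protocol wording, a short briefing of the session staff, study-physician time per event, and missed sessions while clearance is pending (1 per week in Arm 1, 3 per week in Arm 2). A 2-week hold alone keeps a participant within the adherence definition. Longer holds reduce attendance further, and more than 5 missed sessions in Arm 1 or 15 in Arm 2 fall below it. No added participants and no new scheduled visits are needed.
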